### Baseline and follow-up oral examinations

Baseline (T0) and follow-up examinations (T1, T2, T3) will be conducted in each centre at the appointed dental clinic/s (including remote acquiring of interview data if possible and when applicable) by an examiner (E) previously trained in the ICDAS visual caries criteria [35] and in the CCI steps 1D, 2D and 3D [9]. The caries management (4D) will be delivered by external trained dental practitioner/s (DP). These steps are detailed in Fig. 2.

For 1D, remote combined with in-office assessment will be conducted with parents, including social/medical/behavioural risk factors (6 items); protective factors (3 items), and oral hygiene (3 items) and dietary (5 items) oral-health behaviours [3, 9, 10, 29, 31–34, 36]. Clinical risk factors (5 items) will be assessed in the dental clinic with the children, as 2D assessments. After assessing dental biofilm (Silness and Löe modified, [37]) , the other clinical assessments are conducted after toothbrushing, with the aid of a WHO probe and drying tooth surfaces and/or removing any dental biofilm only with cotton rolls/gauze (without using compressed air/water). Assessments at the tooth-surface level include: (1) caries lesions staging and activity assessment using the visual ICDAS-merged Epi criteria (Sound, Initial, Moderate microcavity/shadow, Extensive) active/inactive [35], and (2) presence and status of fillings (Optimal, Acceptable or Not acceptable) and sealants (Optimal or Not acceptable), modified from Cvar and Ryge [38], and at the tooth-level: (1) missing due to caries; (2) tooth close to exfoliation, and (3) dental sepsis as a clinical consequence of untreated caries, with the PuIpal Involvement-Roots-Sepsis Index (prs/PRS) modified from the PUFA Index [39] with/without toothache. Routine bite-wing radiographs are not included and only used in specific cases based on clinical need, not as part of the study protocol. For 3D, after synthesis of information from steps 1D and 2D the examiner conducts the personalised care plan, jointly with the child’s parent and the external DP. At the individual-level, a designed matrix based on CCI [9] weighs up the risk and protective factors against each other, classifying the patient’s caries risk into low or high, with a respective 9-month or 3-month risk recall interval. Another matrix, taking into account the COM-B behaviour model [29] weighs up the adequate vs. inadequate oral hygiene and dietary habits behaviours against each other, classifying the patient’s oral-health behaviour into adequate, inadequate or very inadequate. The individual-level risk management decisions will include homecare and clinical approaches/interventions, according to CCI and adapted for the pandemic (with non-AGP and including remote appointments when possible), including implementing a short behaviour-change tool. At the tooth-surface level, according to the synthesis of the clinical assessments defined in 2D, the type of care is defined per surface with non-AGP as: none, active monitoring (AM), non-operative care (NOC), tooth-preserving operative care (TPOC), and at the tooth-level as endodontics or extraction [9, 9].

T0 and T3 include full 1D, 2D and 3D assessments. For intermediate T1 and T2 follow-ups, in 1D, all receive full oral-health behaviour reassessment, while risk is fully assessed only in patients previously classified as high-risk; in low-risk, only four risk/protective factors are reassessed (twice-a-day toothbrusing with ≥ 1000 ppm F, daily free-sugar intake above 50 g, dental biofilm and presence of new caries lesions). For 2D, all patients are clinically examined only for the latter. Subsequent 3D is derived. If in T1 or T2 the patient’s risk gets classified opposite to their previous assessment, both the recall interval and the reassessment are adjusted accordingly.

Parents’ and dentists’ acceptance of dental care will be assessed by an external researcher at T1, using designed TEI questionnaires (modified from Newton & Sturmey [40]).

Costs will be assessed in terms of duration and number of appointments regarding the type of care received (assessment/reassessment; individual level: risk/behavioral management, recall; tooth-surface level: NOC, TPOC;) and taking into account if the activity has been conducted solely by the examiner/CD, solely by a hygienist or both together, and country-level economic variables will be described [41–43].

Dropout criteria of a child from the study will include: (1) voluntary withdrawal from the trial by the patient/parents; (2) not attending the reassessments and in-office/remote appointments after three phone/message reminders.

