## Methods/design

The design and report of this clinical trial protocol follows the Standard Protocol Items: Recommendations for Interventional Trials (SPIRIT) statement (Additional file 1). The study received approval from the Research Institutional Ethical Committee in Universidad El Bosque (PCI 2019-10718).

This is a 12-month multicentre single-group interventional study that aims at assessing in children the caries-control effectiveness of a pandemic-adapted CCI protocol (non-AGP and reduced in-office appointments’ time). The outcomes include primarily, tooth-level control of caries progression, and secondarily, child-level control of caries progression and caries risk; parents’ and dentists’ acceptability of care, and improvement in children’s oral health behaviours. Data will be collected in the 21 centres that agreed to participate, which are located in Argentina [2], Brazil [1], Colombia [7], Dominican Republic [1], France [1], Mexico [1], Perú [1], Portugal [1], Russia [1], The Netherlands [1], United Kingdom [1], United States [2], and Uruguay [1].

The study phases are based on the CCI 4D cycle (Fig. 1) and include: (1) a baseline examination (T0), corresponding to CCI steps 1D, 2D and 3D to be conducted by the examiner (E); (2) the basic management and intermediate care (CCI step 4D) to be conducted by the dental practitioner/s (DP); (3) two follow-up assessments during the 12-month care period: T1, at 5–5.5 months (3 months after end of basic management care) (E); T2, at 8.5 months, and (4) a final re-assessment at 12 months (T3) (E). The study flowchart is shown in Fig. 2.

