### Outcomes

#### Primary health outcome

Mean number of tooth surfaces with avoidance of caries progression (ICDAS-merged Epi severity and/or activity).

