For the analyses at the tooth-surface level, we will exclude teeth that needed a treatment involving AGP (endodontic treatment, surgical extraction, etc.). Caries progression has been defined for this study in terms of a change from the decided and delivered tooth-surface level care (T0, after the 4D basic management) to the tooth-surface level status at the 12-month follow-up (T3) (Fig. 2), as follows: (1) from a sound surface to a caries lesion, a sealant, a filling, or a missing tooth; (2) from a sealant to a caries lesion, a filling, or a missing tooth; (3) to a more severe caries score and/or an active status (or remaining active), and (4) from a filling to a caries lesion or a missing tooth. The severity/activity caries progression will be firstly assessed through descriptive analyses (number of subjects/surfaces) and a comparison in the number of active lesions at 1 year versus baseline will be applied (Wilcoxon test or paired *t* test based on results of the Shapiro Wilk normality test). Multilevel logistic regression will also be used for the surface level data analyses, exploring the clustering of surfaces within individuals, to estimate the association among characteristics variables and the outcomes.

Parents’ treatment evaluation inventory: Comparisons of parents’ treatment acceptability will be conducted between participants classified in baseline as low vs. high risk using Independent *t* test.

Dentists’ treatment evaluation inventory: The dentists’ treatment acceptability will be described.

Oral-health related behaviour classification will be compared between assessments (T0, T1, T2, T3) and between high and low-risk patients using *t* test.

The level of significance considered for all tests will be 5%.

Analyses to handle protocol non-adherence and missing data: Data of patients who leave before the end of the study will be handled separately. A *t* test analysis will be conducted to compare the baseline mean number of surfaces with caries experience (ICDAS-merged Epi dmfs/DMFS) [35] of those children who left the study during the 1-year follow-up period with that of those who remained in the study. If they’ve left after T1 and or T2, their parents TEI will be also compared with that of those who remained, as well as the children’s oral-health behaviour classification, and the caries progression.

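### A new lesion on a sealed or filled surface that is re-sealed, re-filled or sealed over before T3 meets none of the four progression rules, so the primary outcome scores it as progression avoided

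*Protocol article*

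**What the plan says.** The primary outcome (Protocol article, Primary health outcome) is "Mean number of tooth surfaces with avoidance of caries progression (ICDAS-merged Epi severity and/or activity"), so it is the complement of whatever counts as progression.

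The Statistical analysis plan section defines progression as a change between two states only, from the care decided and delivered at baseline ("T0, after the 4D basic management) to the tooth-surface level status at the 12-month follow-up (T3"). The rules that matter here are:

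- Rule 1, sound surfaces: "1) from a sound surface to a caries lesion, a sealant, a filling, or a missing tooth".
- Rule 2, sealed surfaces: "from a sealant to a caries lesion, a filling, or a missing tooth".
- Rule 4, filled surfaces: "4) from a filling to a caries lesion or a missing tooth".

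Rule 3 covers lesions that become more severe, become active or stay active.

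Between those two states the protocol looks for disease and treats it. Under Baseline and follow-up oral examinations, the last item on the T1/T2 reassessment list is the presence of new caries lesions, and "For 2D, all patients are clinically examined only for the latter. Subsequent 3D is derived". Under Methods/design, the dental practitioner delivers "the basic management and intermediate care (CCI step 4D) to be conducted by the dental practitioner/s (DP"). The Interventions section allows surface-level care throughout the 12 months, and Tables 1 and 2 include ART sealants and ART restorations among the options.

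**The concern.** The plan finds a new lesion at an interim visit, may treat it, and then scores only the treated state. On a surface that began the scoring interval sealed or filled, re-treatment can restore the starting category, and the lesion then leaves no trace in the outcome.

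The rules themselves show that disease treated in the interval is meant to count. Rule 1 counts a sound surface that ends as a sealant or filling, and rule 2 counts a sealed surface that ends as a filling. A new lesion that is sealed therefore counts on a sound surface and does not count on one that was already sealed.

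The affected surfaces include those the study itself sealed or restored during basic management. Whether a lesion is lost depends on whether and how a centre re-treats before T3, so the 21 centres are not scored on a single footing. With one group, there is no comparator in which the same error might partly cancel.

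**Working it through.** **Step 1: apply the four rules to each path through an interim lesion.**

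| After basic management | T1 or T2 | T3 | Rule met | Scored as |
|---|---|---|---|---|
| Sound | new lesion | sealant | 1 | progressed |
| Sound | new lesion | filling | 1 | progressed |
| Sealant | new lesion | filling | 2 | progressed |
| Sealant | new lesion | lesion still present | 2 | progressed |
| Filling | new lesion | lesion still present | 4 | progressed |
| Sealant | new lesion | sealant | none | avoided |
| Filling | new lesion | filling | none | avoided |
| Filling | new lesion | sealant | none | avoided |

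The last three rows are the gap. No text carries a T1 or T2 lesion into the primary outcome.

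**Step 2: check whether another outcome closes it.** Filling or sealant failure is listed under Secondary health outcomes as part of a subject-level proportion. The Statistical analysis plan compares it between T0 and T3. It is separate from the surface count and does not feed the primary outcome.

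**Step 3: size.** The protocol gives no figure for this and none of the rates needed, so there is nothing to reproduce. With every input assumed, let

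- k = sealed or filled surfaces per child after basic management, 2 to 8;
- p = share of these with a new lesion found at T1 or T2, 2% to 10%;
- h = share of those lesions that end in one of the three unscored states, 50% to 100%.

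Missed progression per child = k × p × h.

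- Low: 2 × 0.02 × 0.5 = 0.02 surfaces.
- Middle: 4 × 0.05 × 1 = 0.20 surfaces.
- High: 8 × 0.10 × 1 = 0.80 surfaces.

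Sealed surfaces that are later filled do not belong in h, because rule 2 already counts them. If h is below 50%, which the care tables allow, the result falls towards zero.

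**The case against.** The strongest reply is that the gap is narrow, and that is correct. A reader might infer that interim disease is lost on every surface that starts sealed or filled. The documents do not support this. Rule 2 counts sealant to filling. Tables 1 and 2 also manage many lesions without a sealant or restoration, by active monitoring, fluoride varnish or SDF; on a sealed or filled surface, such a lesion still present at T3 is counted.

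A reader might also take a figure from the visit schedule. T1 at 5–5.5 months is 3 months after basic management, which therefore ends at 2–2.5 months. If lesions arose evenly, (8.5 − 2)/(12 − 2) = 65% or (8.5 − 2.5)/(12 − 2.5) = 63% would exist by T2. This is the share that could be found before T3, not the share hidden, because it says nothing about detection or the type of re-treatment. Nor is the 0.8-surface difference (2.1 − 1.3) in the sample size section a valid yardstick: it is the between-arm contrast of the abandoned randomised trial, and this study has no such contrast.

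A third objection concerns the remedy. Counting any lesion seen at any visit on any surface would turn early lesions on sound surfaces that reverse by T3 into progression. The Background treats such reversal as possible, so that rule would change what is estimated. This objection stands, and the fix below leaves sound surfaces alone.

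Finally, a separate analysis plan might be thought to settle the matter. But the article states the definition in full, so a plan that follows it inherits the gap.

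**Conclusion.** The point holds for three paths: sealant re-sealed, filling re-filled, and filling sealed over, each after a new lesion found at T1 or T2. As written, the primary outcome scores all three as progression avoided, and the child-level progression proportion can be affected in the same way.

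The direction is certain: on these paths the error can only make caries control look better. The size is not known. The range of 0.02 to 0.80 surfaces per child rests entirely on assumed rates, and the true figure could be close to zero. Nothing in the documents shows that a conclusion of the study would change. The case for correcting the rule is that the bias runs one way, depends on centre practice, and is inconsistent with how rules 1 and 2 treat the same kind of event.

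**What to change.** In the progression definition in the Statistical analysis plan section:

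- Add to rules 2 and 4 that a surface sealed or filled after basic management also counts as progressed if a new caries lesion was recorded on it at T1 or T2 and it was then re-sealed, re-filled or sealed over before T3.
- Apply the same rule to the child-level progression outcome.
- Leave rule 1 for sound surfaces unchanged, so that early lesions that reverse by T3 are not newly counted.
- Keep the two-point comparison of T0 (after basic management) with T3 as a sensitivity analysis. The difference between the two results then measures the size of the problem directly.

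The cost is small but not nil. The T1/T2 examination for new lesions is already planned, and data go to the data management team at each time point. However, the protocol describes full clinical assessment only at T0 and T3, so the T1/T2 new-lesion record must identify the surface and be linked to any re-treatment. The progression figure will be somewhat less favourable. No care, visit or sample size changes.

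One limit: a lesion left as a lesion at baseline that worsens and is sealed or filled before T3 is not named in rule 3 either, and this change does not reach it.

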### Sample size and recruitment

The sample size was determined based on the sample size calculated for the previous randomized clinical trial, which was based on Curtis et al. [42]. We decided to use the mentioned study, even though it is on adults, as it is one of the very few available studies that deals with the management of caries using an updated system, similar to CariesCare International, taking into consideration both the care of caries lesions according to their severity and activity status, as well as of the individual caries risk. The results show differences in averages of surfaces with caries progression, between two preventive care schemes. The Whitehead sample size calculation formula was taken into account, with type-I error: 0.05, type II error: 10%, standard deviation 2.5, expected average of the first group 1.3 and expected average of the second group 2.1.

For the current study, as there is no control arm, with the leader team it was decided to include half of the previous RCT sample size. Thus, the sample size calculation of this single-group interventional study corresponded to 206 3–5 and 6–8 years old children, increasing to a total of 258 after including a 25% dropout. As the sample calculation per arm in each centre in the previous study corresponded to 20 participants, in this single-interventional study we are asking each centre to recruit 27 patients. These would correspond to 567 participants in total if the centres [21] finish the study with 27 participants each.

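### The dropout rule counts missed visits with no exception for T3, so it can remove children whose primary outcome could still be measured

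*Protocol article*

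**What the plan says.** The Protocol article, section Baseline and follow-up oral examinations, gives two criteria: "Dropout criteria of a child from the study will include: (1) voluntary withdrawal from the trial by the patient/parents" and "2) not attending the reassessments and in-office/remote appointments after three phone/message reminders". Both concern leaving the study, not only leaving treatment. The same section lists the follow-up examinations: "Baseline (T0) and follow-up examinations (T1, T2, T3) will be conducted in each centre". It also states that "T0 and T3 include full 1D, 2D and 3D assessments"; T1 and T2 carry only a reduced clinical examination.

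The primary outcome is "Mean number of tooth surfaces with avoidance of caries progression (ICDAS-merged Epi severity and/or activity". The section Statistical analysis plan defines progression as "a change from the decided and delivered tooth-surface level care (T0, after the 4D basic management") and "to the tooth-surface level status at the 12-month follow-up (T3").

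That section also says that data of children who leave early are treated apart from the rest. Leavers are compared with remainers on baseline caries experience. Those who left after T1 and/or T2 are also compared on parents' acceptability scores, behaviour classification and caries progression. The section Sample size and recruitment plans 206 children, "increasing to a total of 258 after including a 25% dropout".

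**The concern.** Non-attendance stands beside voluntary withdrawal as a way out of the study, and the visits it covers include T1 and T2. Neither visit enters the definition of progression. A child can therefore miss an interim visit, remain willing to be seen at 12 months, and still be classed as a dropout.

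T1 and T2 are also occasions for care: varnish, reassessment and behaviour support. Children who miss them have received less of the package. If they leave the analysis set, the result describes children who attended rather than children to whom the programme was offered. The stated aim is effectiveness, and with one arm there is no control group with similar attrition to compare against.

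**Working it through.** **1. The plan's own figures.** Inputs from Sample size and recruitment: two-sided alpha 0.05 (sidedness from Statistical analysis plan), power 90%, SD 2.5, means 1.3 and 2.1.

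- Per group: 2 × (1.960 + 1.282)² × 2.5² / 0.8² = 205.2, rounded up to 206. Two arms give 412, and half of that is 206. This reproduces.
- With dropout: 206 × 1.25 = 257.5, rounded to 258. This reproduces.
- Recruitment target: 21 × 27 = 567. This reproduces.
- After 25% loss: 258 × 0.75 = 193.5, and 567 × 0.75 = 425.25.

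**2. Visits the rule covers against visits the outcome uses.**

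| | T0 and basic management | T1 | T2 | T3 |
|---|---|---|---|---|
| Non-attendance can count towards dropout | basic-management appointments, yes | yes | yes | yes |
| Full assessment | yes (T0) | no | no | yes |
| Enters the progression definition | yes (status after delivered care) | no | no | yes |

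The T1 and T2 columns are the mismatch: the rule covers these visits and the outcome does not use them.

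**3. One child followed through.** A child completes basic management, and the family does not attend T1 after three reminders but does not withdraw. On a plain reading the child is now a dropout. The article provides no T3 examination for such a child. The planned comparison of progression for those who left after T1 or T2 cannot then be made as progression is defined, because it needs T3 status.

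**4. Size, as illustration only.** The documents give neither the share of dropouts who could be examined at T3 (call it s) nor how much more they progress (call it D). Both are assumed here. With 25% dropout:

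- Children with T3 data if such children are kept: N × (0.75 + 0.25s).
- Their share of all examinable children: f = 0.25s / (0.75 + 0.25s).
- Understatement of mean progressing surfaces if they are left out: f × D.

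| s | T3 data, N = 258 | T3 data, N = 567 | f | f × 0.4 | f × 0.8 |
|---|---|---|---|---|---|
| 0% | 193.5 | 425 | 0 | 0 | 0 |
| 20% | 206 | 454 | 0.063 | 0.03 | 0.05 |
| 40% | 219 | 482 | 0.118 | 0.05 | 0.09 |
| 60% | 232 | 510 | 0.167 | 0.07 | 0.13 |

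For scale, the standard error of a mean with SD 2.5, ignoring clustering by centre, is 2.5/√193.5 = 0.18, or 2.5/√425 = 0.12. The bias depends on s and D, not on N, so larger enrolment does not reduce it. D = 0.8 merely borrows the distance between the two planning means, which come from a study in adults. Nothing links those means to attenders and non-attenders. The primary outcome counts surfaces that avoid progression, so, for a given number of surfaces, the same selection would overstate it.

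**The case against.** The rule joins reassessments and appointments with *and*, uses the plural, includes remote contact, and applies only after three reminders. It can be read as describing a family that has stopped responding altogether, which is ordinary loss to follow-up. Leavers' data are analysed apart, not deleted. The section Interventions sets out reminders and a remote channel to support retention. The full protocol may say more about inviting lapsed families to T3.

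Part of this stands. A reader might infer that one missed visit removes a child and that the rule therefore discards primary data as a matter of course. The text does not support that: it does not say how many missed visits count, and on the narrow reading few children would be affected. A reader might also infer that the protocol expects pandemic closures to cause missed interim visits. The Discussion speaks of ethical restrictions that forced the single-group design and of uncertain timing at the centres, not of missed T1 or T2 visits. Nor can a loss of precision be asserted: if 567 enrol, about 425 remain after 25% loss, well above 206.

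Two things remain. The article states the rule and leaves it open to different application across 21 centres. And no later analysis plan can recover T3 examinations that were never done.

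**Conclusion.** The point holds in limited form. The dropout rule sets no number of missed visits and makes no exception for a child who can still attend T3, while progression uses only the status after basic management and at T3. Followed on a plain reading, it can lose obtainable primary outcomes from less adherent children and move the result towards attenders.

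The size is not derivable from the documents. Under the assumed ranges above, the understatement runs from nothing to about 0.13 progressing surfaces, below one standard error at 193.5 children and about one at 425. It rests on two conditions: that some children miss interim visits yet remain examinable at T3, and that they progress differently from attenders. This is a cheap improvement to the wording, not a defect that invalidates the design.

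**What to change.** In Baseline and follow-up oral examinations, limit dropout from the study to withdrawal of consent or assent, or failure to attend T3 after three reminders. Record missed T1, T2 or intermediate appointments as non-adherence, and still invite these children to T3.

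In Statistical analysis plan, include in the primary analysis all children who have a post-basic-management status and a T3 examination. Report children with incomplete basic management separately, because they may lack the defined starting status. Show attenders of all visits as a secondary analysis.

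The cost is a change of wording, which goes to the ethics committee as an amendment, and some extra effort to contact families for T3. The result may be less favourable if poor attenders do worse. Nothing in the care delivered changes.
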